#### Wastewater samples

2.7.2

Active surveillance will be carried out for the presence of MDR microorganisms in the wastewater from selected NHs. Simultaneously, phenotypic and molecular characterization will be performed.

From each wastewater sample, 50 mL aliquots will be obtained and centrifuged at 12,000 rpm for 10 min. From the bacterial pellet obtained, an amount equivalent to 5 μL will be taken and resuspended in 500 μL of nucleic acid-free water. Then, 10 μL will be taken and quantitatively plated on Columbia blood agar. For the detection of MDR bacteria, 10 μL will be taken and planted in selective media. Then, the same process described for clinical samples will be performed for phenotypic characterization. For molecular characterization, the MDR Direct Flow Chip® system (Vitro S.A., Granada, Spain) (29) will be used, based on a polymerase chain reaction (PCR) and reverse hybridization system that allows the detection of five bacterial species (*S. aureus, P. aeruginosa, E. coli, K. pneumoniae* and *A. baumannii*), as well as 56 genetic determinants of antibiotic resistance.

### Antimicrobial concentration in wastewater samples

2.8

First, the sample will be centrifuged 20 min at 3,000 rpm and at a temperature below 15 °C. Then, it will be divided into two aliquots and adjusted to pH 2 or 7 for extraction of the following antimicrobials:pH 2: amoxicillin, methylated amoxicillin, amoxicillin (5R,5S), clavulanic acid, cefixime, clindamycin, clindamycin sulfoxide, levofloxacin, ciprofloxacin, and moxifloxacin will be extracted. The last three will also be extracted at pH 7.pH 7: azithromycin, clarithromycin, metronidazole, hydroxy-metronidazole, sulfamethoxazole, and trimethoprim will be extracted.

Compound extraction will be performed using solid-phase extraction (SPE) with Oasis HLB cartridges (6 cc, 200 mg; Waters, Labtim, Croatia). Finally, the extract will be dried under a stream of nitrogen and reconstituted with the mobile phase. The resulting extract will be refrigerated and transported to the Institute of Environmental Assessment and Water Research of the Spanish National Research Council (IDAEA-CSIC).

There, the analysis and quantification of antimicrobials and metabolites will be carried out by means of an Orbitrap-Exactive HCD (Thermo Fisher Scientific, Bremen, Germany) mass spectrometer equipped with a heated electrospray source (H-ESI II), a Surveyor MS Plus pump and an Accela Open AS autosampler which will be kept at 10 °C (Thermo Fisher Scientific, San Jose, California). The chromatographic separation will be performed on a reversed-phase Luna C18 column (150 × 2.0 mm, 5 μm, Phenomenex, Torrance, CA, USA) preceded by a C18 guard column (4 × 2.1 mm, Waters, Milford, MA, USA). The mobile phase will be composed of 0.1% HCOOH in water as solvent A and 0.1% HCOOH in ACN as solvent B at a flow rate of 200 μL min^−1^. The linear gradient elution program will be: 5% up to 95% ACN in 15 min. This percentage will then be maintained for 1 min, and after that the LC system will return to initial conditions for 10 min. The injection volume will be 10 μL. The MS analyses will be carried out in positive and negative electrospray ionization (ESI). Data will be acquired in full-scan mode in a mass range of *m/z* 100–1,000. A maximum of ±5 ppm mass accuracy extraction window will be applied for peak identification. The analytes will be quantified using TraceFinder 5.1 software (Thermo Fisher Scientific, Bremen, Germany).

The analytical methodology for analysis of antimicrobials in wastewater samples is shown in Figure 3.

**Figure 3 fig3:**
[figure not shown]
Analytical methodology for analysis of antimicrobials in wastewater samples.

### Statistical analysis

2.9

A descriptive analysis will be performed. Continuous variables will be expressed as measures of central tendency and dispersion, such as mean ± standard deviation or median and interquartile range, depending on the distribution. Categorical variables will be expressed as absolute and relative frequencies.

Interrupted Time Series Analysis (ITSA) will quantify changes in the level (immediate effect) and trend (sustained effect) of outcomes associated with implementing the web platform, considering the study’s longitudinal and ecological nature. ITSA will be performed using a segmented regression model to estimate four parameters: baseline level, baseline trend, the change in level immediately following the intervention, and the change in trend following the intervention. Seasonal adjustment will be applied to those time series in which seasonality were detected. The model incorporates an autoregressive term to account for the autocorrelation present in the time series data. To assess variability and the overall effect across different centers, we will use a linear mixed model (LMM) for repeated measures that includes a random intercept for center. Potential confounders will be managed as fixed effects covariates. *Post hoc* comparisons of estimated marginal means will be performed with the Bonferroni correction applied to adjust for multiple comparisons.

We will evaluate the correlations between the presence of MDR microorganisms and their resistance profiles in wastewater, clinical, and carrier screening samples. We will also evaluate the correlations between antimicrobial concentrations in wastewater and consumption data from centers. We will assess the strength and direction of these correlations using the appropriate Pearson or Spearman correlation coefficient. Then, we will perform univariate and multivariable linear regression analyses to further explore the relationships.

All statistical analyses will be performed using two-tailed tests in IBM SPSS Statistics and R statistical software. A *p*-value of less than 0.05 will be considered statistically significant.

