#### Sample size

2.3.2

The sample size has been calculated based on the results of the multicenter study ‘PROA-SENIOR’ (13). Considering an intraclass correlation coefficient of 0.21, a coefficient of variation between center for total antimicrobial consumption (the main variable) of 0.41, and an average of 110 residents per center, with an alpha risk of 5%, a power of 80%, and a detection of the effect size of 20%, the required sample size is 9 centers. Adding a 10% loss, the minimum sample size obtained is 10 NHs. For the wastewater analysis, three participating NHs will be selected.

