To evaluate the impact of ASPs, previous studies have analyzed changes in the number of prescriptions or, less frequently, in the DDD as an internationally accepted measure of antibiotic use (8). Indicators of antimicrobial resistance are infrequently reported, and the outcomes vary among studies, although common outcomes include *C. difficile* detection, MRSA and/or MDR gram negative bacterial infections (13, 34, 40, 41). Similarly, clinical outcomes (e.g., hospitalization rates, mortality, and clinical adverse events) are reported in fewer than one-third of ASP studies in NHs, according to a recent systematic review (41). The EduFAST project will collect antimicrobial consumption, resistance, and clinical indicators, allowing for comparison with the results of previous interventions. But also, EduFAST project will aim to evaluate the environmental impact by studying the concentration of antimicrobials, MDR microorganisms, and resistance genes in wastewater. Currently, there is little evidence regarding the impact of antibiotic use on the microbiological composition of wastewater in NHs and the potential use of wastewater for surveillance purposes of antimicrobial consumption and microbial resistance (42, 43). This project will therefore provide relevant information on this subject and contribute an environmental indicator that has not been included in ASPs previously.

The primary limitation of the study is its quasi-experimental, before-and-after design. However, given the recommendations of national and international organizations to promote the implementation of ASP in all healthcare settings and the existing evidence of its positive impact, proposing a clinical trial with a non-intervention comparison group would raise significant ethical concerns. Another limitation is the heterogeneity among NHs, particularly with regard to size, resident profiles, infrastructure, and human resource availability. This could lead to variability in implementation and affect adherence to the recorded variables. For this reason, we have implemented a system of close monitoring and follow-up of platform usage metrics and indicators, as described in the Materials and Methods section. Second, linear mixed models will be used to evaluate the intervention’s impact and handle center effects in this multicenter study.

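### The mixed model for the overall effect names only a random intercept for center, so its standard error is too small to the extent that the platform's effect differs between centers

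*Protocol article*

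**What the plan says.** Section 2.9 (Statistical analysis) describes two models. The interrupted time series analysis is a segmented regression with baseline level, baseline trend, level change and trend change. Of it the section says: "The model incorporates an autoregressive term to account for the autocorrelation present in the time series data". On season it says: "Seasonal adjustment will be applied to those time series in which seasonality were detected".

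The second model has its own purpose, "To assess variability and the overall effect across different centers", and for this "we will use a linear mixed model (LMM) for repeated measures that includes a random intercept for center". Confounders enter as fixed effects, and Bonferroni-adjusted comparisons of estimated marginal means follow. No center-specific level change, trend change or phase effect is named.

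The Discussion lists differences between homes in size, residents, infrastructure and staffing and adds: "This could lead to variability in implementation and affect adherence to the recorded variables". It then relies on linear mixed models to "handle center effects in this multicenter study".

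**The concern.** A random intercept has one variance component, the spread of baseline levels. It contains nothing from which the spread of the platform's effect could be estimated, because every center is given the same effect.

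If the true effects differ, the overall effect is an average over about 10 center-specific effects, and its uncertainty cannot fall below what 10 such effects allow. The random-intercept model counts mainly month-to-month noise, spread over some 240 center-months. The interval for the overall effect then becomes too narrow and the test rejects too often. The protocol itself gives a reason to expect such differences, and the model it names as the remedy addresses baseline differences only.

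**Working it through.** **Inputs from the protocol.** Required centers 9, with 10% loss: 9 / (1 − 0.10) = 10, which reproduces the stated minimum (section 2.3.2). How the 9 was obtained is not stated, and nothing here depends on it. Same section: "Considering an intraclass correlation coefficient of 0.21, a coefficient of variation between center for total antimicrobial consumption (the main variable) of 0.41". Intervention phase of 12 months (Abstract). Twelve baseline months are stated only for wastewater (section 2.6.2) and are assumed here for the monthly series.

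**Assumed.** Residual SD σ = 0.41 × √(1 − 0.21) = 0.364 of mean consumption, so σ² = 0.1328. This treats 0.41 as a total coefficient of variation, although the protocol calls it between-center. The between-center SD of the effect, τ, is taken as 0, 0.10, 0.15 and 0.20 of mean consumption. Residuals are independent and the true mean effect is 0.

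**Formula.** Let c be the variance factor of the estimate within one center.
- True variance of the overall effect: (τ² + cσ²) / 10.
- Variance reported by the random-intercept model: c(σ² + kτ²) / 10. Here k is the part of the effect variation that leaks into the residual: 9 × 6 / 229 = 0.236 for the before-after mean and 9 × 6 / 227 = 0.238 for the segmented model.
- SE ratio r = √(reported / true). False-positive rate ≈ 2Φ(−1.97 r).

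**Before-after mean**, c = 1/12 + 1/12 = 0.1667, cσ² = 0.0221:

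| τ | reported × 10 | true × 10 | r | false positives |
|---|---|---|---|---|
| 0 | 0.0221 | 0.0221 | 1.00 | 5% |
| 0.10 | 0.0225 | 0.0321 | 0.84 | 10% |
| 0.15 | 0.0230 | 0.0446 | 0.72 | 16% |
| 0.20 | 0.0237 | 0.0621 | 0.62 | 22% |

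**Segmented level change**, c = (1/12 + 6.5²/143) + (1/12 + 5.5²/143) = 0.674, cσ² = 0.0895:

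| τ | reported × 10 | true × 10 | r | false positives |
|---|---|---|---|---|
| 0 | 0.0895 | 0.0895 | 1.00 | 5% |
| 0.10 | 0.0911 | 0.0995 | 0.96 | 6% |
| 0.15 | 0.0931 | 0.1120 | 0.91 | 7% |
| 0.20 | 0.0959 | 0.1295 | 0.86 | 9% |

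A simulation of 40,000 trials per setting with these inputs gives 10%, 16% and 23% for the mean and 6%, 7% and 9% for the level change. A t test on the 10 center-specific estimates stays at 5% throughout.

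**Other assumptions.** With residual SD 0.20 the inflation is larger. At τ = 0.10 it is 14% to 20% for the mean and about 8% to 9% for the level change. At τ = 0.20 it is 28% to 39% and 10% to 17%. If trends also differ between centers and an AR(1) is estimated, the level-change SE is nearly right (ratio 0.94 to 1.03), but the before-after SE stays too small (0.60 to 0.75).

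**Seasonality.** For an annual cycle of amplitude A peaking in January (assumed) and left out of a 12+12-month segmented model, least squares shifts the level change by −0.50A for a July start and +0.50A for a January start. With A = 10% this is 5 points, a quarter of the 20% effect in the sample size. A two-parameter harmonic test finds that cycle with power of about 11% in one center (A/SD = 0.10/0.364 = 0.27) and about 67% in a pooled series (0.10 / (0.364/√10) = 0.87). Putting the harmonic in every series raises the variance factor of the level change from 0.674 to 1.518, that is 2.25-fold. Longer baselines reduce the bias: −0.15A with 18+12 months from January 2024.

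**The case against.** The strongest reply is that the defect is conditional and partly a matter of brevity. Several parts of it stand.

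- **The standard error.** A reader might infer that it is simply wrong. It is not: with one common effect and independent residuals it is correct. The protocol expects variable implementation but gives no SD for the effect.
- **Autocorrelation.** A reader might also infer that the mixed model ignores it. With an omitted autocorrelation of 0.3, the before-after test would reject in 14.6% of trials even at τ = 0. But the model is described as one for repeated measures, directly after the autoregressive term is introduced, and the text never says that it lacks a residual structure. Those figures are therefore not part of this point.
- **The word variability.** It could mean variability of the outcome, which an intercept variance does estimate.
- **The contrast.** The level and trend changes are the stated time series parameters, and for the level change the inflation is modest. The larger figures apply to a before-after mean, which the marginal-means comparisons suggest but do not spell out.
- **Detail left to an analysis plan.** The degrees-of-freedom method and convergence rules belong there, and their absence is no fault. The random-effects structure is different: the article states one, and the one stated does not fit the heterogeneity that the Discussion says the model will handle.

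**Conclusion.** The point holds in conditional form. The only random effect named for the model of the overall effect captures baseline differences and not differences in the platform's effect, while the protocol anticipates the latter. To the extent that they exist, the overall effect is reported too precisely. Under the stated assumptions the false-positive rate is about 10% to 22% for a before-after mean and 6% to 9% for the level change, against about 5% with a homogeneous effect and independent residuals. These are illustrations: τ, the residual SD and the 12-month baseline for consumption are not given.

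Seasonal adjustment on detection is a weaker, secondary issue. It can leave bias in the level change. It does not follow that a harmonic must enter every series, because the 2.25-fold variance is a real price. The sign of the bias also depends on the start of the intervention, which section 2.1 puts in July 2025 and section 2.2 at the end of 2025. Those two statements must be reconciled.

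**What to change.** State the mixed model for the center-month data as follows.

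1. Fixed effects: the segmented terms already listed for the time series analysis, plus the planned covariates.
2. Random effects: center intercept and center-specific level change (or center-by-phase). Add a center-specific trend change if the model converges.
3. Residuals: the autoregressive structure already stated for the time series analysis, within center.
4. Kenward-Roger or Satterthwaite degrees of freedom, given about 10 centers.
5. Report the between-center SD of the effect.
6. Fallback: a one-sample t test on the center-specific estimates.
7. Season: keep the present rule and add a harmonic-adjusted model as a pre-specified sensitivity analysis.

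The work is plan wording and standard R code, and no new data are needed. The statistical cost is wider intervals. For the before-after mean with the fallback t test (critical value 2.262 on 9 df), the 95% half-width is 2.262 × √(0.0321/10) = 0.128 at τ = 0.10, against 1.97 × √(0.0225/10) = 0.093 with a random intercept. At τ = 0.20 it is 2.262 × √(0.0621/10) = 0.178 against 1.97 × √(0.0237/10) = 0.096. If the effect is the same everywhere the price is small: 2.262 × √(0.0221/10) = 0.106 against 1.97 × √(0.0221/10) = 0.093.

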### Study design and period

2.1

This is a quasi-experimental before-and-after interrupted time series study evaluating the implementation of antimicrobial stewardship strategies through a web platform (EduFAST) for healthcare workers in NHs. The project comprises four phases (Figure 1). The preparation and pre-intervention phase were carried out between January 2024 and June 2025. The study is currently in the intervention phase, which began in July 2025 and will continue until 2026. The results are expected in early 2027.

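### The mixed model for the overall effect names no term for monthly variation shared by all homes, so its standard error is too small whenever such variation exists

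*Protocol article*

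**What the plan says.** Section 2.9 of the protocol article describes two analyses of the monthly outcomes.

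- **Segmented interrupted time series (ITSA).** It estimates changes in level and trend. Of this model the article says "The model incorporates an autoregressive term to account for the autocorrelation present in the time series data" and "Seasonal adjustment will be applied to those time series in which seasonality were detected".
- **Linear mixed model (LMM).** Its purpose is given as "To assess variability and the overall effect across different centers", and for that "we will use a linear mixed model (LMM) for repeated measures that includes a random intercept for center". On fixed effects it adds only "Potential confounders will be managed as fixed effects covariates".

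The decision rule is common to both: "All statistical analyses will be performed using two-tailed tests in IBM SPSS Statistics and R statistical software" and "A *p*-value of less than 0.05 will be considered statistically significant". The Discussion repeats that mixed models will serve to judge the impact of the intervention and to deal with center effects, so the LMM is not merely descriptive.

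On timing, section 2.1 describes a single intervention phase, "which began in July 2025 and will continue until 2026". Section 2.2 also describes a single phase but puts its start at the end of 2025. Neither section mentions a staggered start, and the Discussion explains why there is no comparison group without the intervention.

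**The concern.** With one start for the whole project and no control homes, the intervention indicator changes only with calendar time. Anything that pushes all homes up or down in a given month, such as an epidemic wave or a supply problem, is error in the effect estimate that averaging over homes does not remove. A center intercept removes stable differences between homes and nothing else. Once it is fitted, the model treats 10 homes observed in the same month as 10 independent readings of that month.

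The result is false precision in the overall effect. A chance difference between the months before and after the start could be declared a platform effect more often than the 5% rule allows. Recruiting more homes makes the mismatch worse.

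The other terms mentioned do not repair this:

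- Autoregressive residuals within a center leave the homes independent of each other in the same month.
- A seasonal term removes the regular cycle only.
- Letting each home have its own effect does not help, because a shared shock is identical in every home and cancels from the between-home spread.

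**Working it through.** **Inputs**

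- Number of homes J = 10 (section 2.3.2: 9 homes, and 9/(1-0.10) = 10 after the allowance for loss).
- Two-sided test at 0.05 (section 2.9).
- Months: 12 before and 12 after. This is an assumption for the outcome series, because section 2.6.2 gives 12+12 only for wastewater sampling. 18+12 was also run, since January 2024 to June 2025 in section 2.1 is 18 months.
- s, the share of within-home monthly variance common to all homes. The article gives no figure, so a range is used.

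**Formula**

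Write the outcome of home j in month t as center effect + segmented time function + shared month shock (variance sσ²) + own residual (variance (1-s)σ²). In a balanced panel the LMM estimate of any effect that depends on time alone equals the regression of the month means on time. With c the constant from the time design:

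- variance reported by the LMM ≈ cσ²/J
- actual variance = cσ²[s + (1-s)/J] = (cσ²/J)[1 + (J-1)s]

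The standard error is therefore too small by sqrt(D), with D = 1 + (J-1)s, and the actual error of the test is 2[1 - Φ(1.96/sqrt(D))].

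**The plan's own figure first.** At s = 0, D = 1 and the error is 5%, as intended.

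**Results for J = 10.** The simulated columns give the level-change test in the segmented model, with no true effect, independent shocks and 4,000 runs per cell.

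| s | D = 1+9s | sqrt(D) | Error, formula | Simulated, 12+12 | Simulated, 18+12 |
|---|---|---|---|---|---|
| 0 | 1.00 | 1.00 | 5.0% | 5.0% | 4.7% |
| 0.02 | 1.18 | 1.09 | 7.1% | – | – |
| 0.05 | 1.45 | 1.20 | 10.4% | 10.1% | 10.2% |
| 0.10 | 1.90 | 1.38 | 15.5% | 15.2% | 15.6% |
| 0.20 | 2.80 | 1.67 | 24.1% | 23.8% | 24.6% |
| 0.50 | 5.50 | 2.35 | 40.3% | 40.7% | 39.7% |

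Repeat simulations put s = 0.10 at 15-16% and s = 0.50 at 40-42%.

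**Sensitivity**

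- *Nine homes:* the formula gives 14.4% at s = 0.10 and 38.1% at 0.50, slightly lower, as expected with fewer homes.
- *Simple before/after contrast, 12+12:* 15.5% at s = 0.10 and 41.1% at 0.50.
- *Sine/cosine seasonal term added, 12+12:* 16.0% at s = 0.10 and 43.6% at 0.50, so it gives no protection against irregular shocks.
- *Shared shocks autocorrelated at 0.4, 12+12:* 14.9% at s = 0.05, 21.9% at 0.10 and 54.3% at 0.50.

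**Check of the remedy.** Testing the level change against month-to-month variation, with 24-4 = 20 degrees of freedom, gives 4.7-5.7% for s from 0 to 0.50 when shocks are independent. With shocks autocorrelated at 0.3 the same test gives 8-12% for s from 0.10 to 0.50, so it is adequate only without autocorrelation.

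**The case against.** **The size is not in the document.** A reader might infer that the test runs at 16-42% as a matter of fact. The article does not support that. Those figures need 10-50% of within-home monthly variance to be shared, and no such share is reported. If it is 1-5%, the error is about 6-10%. This part of the objection stands.

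**Seasonality does not supply the missing figure.** A seasonal swing of ±20% against a 30% within-home standard deviation would correspond to s = (0.20²/2)/(0.20²/2 + 0.30²) = 0.02/0.11 = 0.18. Neither input is in the article. A regular cycle is also not a random month shock, and section 2.9 plans to adjust for seasonality where it is detected. When that case is simulated, a 12+12 phase-mean contrast rejects in about 3% and a segmented level test with a sine/cosine term in about 5%. The concern rests on irregular shocks alone.

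**The ITSA is not affected in this way.** On a pooled monthly series, shared shocks sit in the residual and the autoregressive term handles their serial correlation. A reader might conclude that the whole impact analysis is invalid, which does not follow. However, sections 2.9 and 3 also give the LMM the overall effect, and nothing says which analysis prevails if they disagree.

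**The article is condensed.** It says the LMM includes a center intercept, and a fuller plan may add more. That is a fair caution. The model is nevertheless specified to the point of naming its random structure, and the named structure is insufficient for this design.

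**A common start is implied, not stated for each home.** Sections 2.1 and 2.2 disagree on the date, and section 2.5 records the number of homes registered each month, which leaves room for staggered registration. Still, both sections describe one study-wide phase, and the analysis is framed as a single before/after break.

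**Conclusion.** The point holds for the LMM as named. With a center intercept as its only stated random term, and an effect identified by calendar time, the standard error of the overall effect is too small for any s above zero, by about sqrt(1+(J-1)s). The direction does not depend on the assumptions, but the size does. With 10 homes, the nominal 5% is about doubled at s = 0.05 and reaches 40-42% only at s = 0.50. These figures assume a common start, a balanced panel and independent monthly shocks; positive autocorrelation raises them. The pooled ITSA with its autoregressive term does not share the defect.

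**What to change.** In section 2.9, do one of the following before the analysis (results are expected in early 2027):

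- **Extend the LMM.** Add a calendar-month random effect crossed with center, with AR(1) correlation across months, and use small-sample degrees of freedom based on the number of months rather than the number of center-months.
- **Or separate the roles.** Take the overall level and trend p-values and intervals from the pooled monthly ITSA with its autoregressive term, and keep the LMM for between-center variability.

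Ordinary least squares on month means with (months - 4) degrees of freedom is enough only if the monthly shocks are not autocorrelated, so it should not be treated as interchangeable with the first option.

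It would also help to reconcile the start dates in sections 2.1 and 2.2 and to state whether all homes started together.

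The cost is one more model term, or one sentence assigning roles, and no new data. The price is wider intervals: with 10 homes and independent shocks, about 1.2 times as wide at s = 0.05 and 1.4 times at s = 0.10, before the further widening from fewer degrees of freedom.
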